#### Edinburgh Postnatal Depression Scale (EPDS)

A questionnaire used to screen for symptoms of depression and anxiety in the postpartum period, containing 10 questions that may be self-administered. A final score ≥ 10 has been defined as the cut-off point of greatest sensitivity in screening. The tool has been validated for use in Brazil.

#### The World Health Organization Disability Assessment Schedule II (WHODAS II)

A 36-item questionnaire used to evaluate the individual's perception of herself and her functional status, consisting of six activity domains related to the woman's routine activities (understanding and communicating, getting around, self-care, getting along with people, life activities in the home/at work and participation in society), on a 6-level scale varying from (1) no difficulty to (6) extreme difficulty/cannot do. Final score varies from 0 to 100 (from best to worst) [25].

#### Neuro-psychomotor development of the child

The Denver Developmental Screening Test II consists of 125 tasks or items organized in the form of tests of 4 general functions: personal-social, fine motor-adaptive, language and gross motor. At the end, a behavior test is applied that helps the examiner subjectively observe the overall behavior of the child and obtain an impression on how the child uses his/her skills.

### Quality control

Quality control procedures will be adopted and include techniques such as reviewing completed forms, checking data entry, repeating data collection for selected medical charts and the use of a detailed manual of operation. Initial quality control of data collection will be performed by the local investigator prior to and during electronic data entry of the forms in order to identify any possible inconsistencies in the data.

A second quality control procedure will be carried out by one of the principal investigators, who will visit the participating centers. At this visit, consistency will be verified between the manual records on file and the data contained in the electronic forms. In addition, a random evaluation will be made of hospital records.

For the quality control of the longitudinal component, 10% of the records at each participating center will be randomly selected at the end of individual data collection and contact will once again be made with the patient in order to verify the data obtained at the first interview. The local investigators will maintain a record of any problems occurring during the study and any queries will be raised with the country coordinator of the project.

### Data analysis

Data analysis will be performed in sub-groups according to the time of occurrence of the near-miss or severe maternal morbidity (in adolescence, older ages or at another time in the woman's reproductive life) and determining cause (hypertension, hemorrhage, abortion or other causes). The rates of maternal near-miss will be calculated for each collaborating center using the WHO maternal near miss approach [5], and frequencies of non-near-miss severe maternal morbidity will be calculated using specific defined diagnoses. General estimates will be calculated together with their respective 95% confidence intervals. The association between organ dysfunction and maternal death will be estimated using odds ratios, likelihood ratio test and their respective 95% confidence intervals. In addition, relative risks will be calculated for sexual dysfunction, postpartum depression, posttraumatic stress disorder, deterioration in quality of life, deterioration in the woman's perception of her own functional status in routine activities, risk of adverse perinatal outcome and risk of impaired neuromotor and weight-height development in the children born from the pregnancy associated with severe maternal morbidity.

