### Specific objectives

• To determine the frequency of maternal near-miss in healthcare facilities of different levels of complexity situated in different regions of Brazil, using the World Health Organization (WHO)'s new set of criteria for near-miss [5];

• To determine the frequency of non-near-miss severe maternal morbidity in these facilities using specifically defined potentially life threatening conditions;

• To evaluate the association between the indicators of organ dysfunction used to define maternal near-miss and the risk of maternal death;

• To determine the frequency of near-miss and non-near-miss severe maternal morbidity according to age-group and specific causes;

• To examine the occurrence of avoidable factors and other factors associated with maternal near-miss;

• To investigate the repercussions of severe maternal morbidity and near-miss on the quality of life of survivors up to six months after the event;

• To investigate the presence of sexual dysfunction, posttraumatic stress disorder and postpartum depression, as well as women's perception of their functional status in routine activities in the six months following an occurrence of severe maternal morbidity.

• To investigate the immediate perinatal outcome and subsequent neuromotor and weight-height development in children born from pregnancies associated with severe maternal morbidity.

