## Methods/Design

This study has two components: a multicenter cross-sectional study and a concurrent cohort study.

The cross-sectional study will be implemented in 27 referral obstetric units in different geographical regions of Brazil, which have already joined the initiative for building a national network for studies on maternal and reproductive health. Over a 12-month period, the principal and local investigators will carry out prospective surveillance and will collect data for the identification of maternal near-miss and non-near-miss cases, severe maternal morbidity (potentially life threatening conditions) and maternal deaths. To determine the number of collaborating centers to be included in the present study, calculation of sample size took into consideration the number of deliveries that would have to be monitored to identify cases of near-miss and maternal deaths. Previous studies have estimated a maternal near miss incidence of approximately 8 cases per 1000 deliveries [24] and a Brazilian maternal mortality ratio of 140 per 100,000 LB. Therefore, a total of approximately 75,000 deliveries would have to be monitored in order to identify around 100 maternal deaths and 600 maternal near miss cases. These numbers are believed to be sufficient to evaluate the use of the new criteria for near-miss established by the World Health Organization in 2009 [5] and to perform analysis allowing for level of complexity of health facility, age group and specific cause.

The study population will consist of all the women admitted to the participating hospitals during the study period in whom organ dysfunction is registered (maternal near-miss, Appendix 1), in whom one of the diagnoses defined as non-near-miss severe maternal morbidity is present (Appendix 2), and those who died or were transferred to another healthcare service because of their bad health condition.

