#### Maternal death

Death of a woman during pregnancy or within a 42-day period following the end of pregnancy irrespective of the duration or localization of the pregnancy, resulting from any cause related to or aggravated by the pregnancy or by measures taken with respect to it; however, not from accidental or incidental causes.

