### Data Collection and Procedures

#### Cross-sectional component

Research assistants, referred to as local coordinators, will review the charts of hospitalized patients on a daily basis in search of cases with one of the conditions identifying severity (Appendix 2). In cases found with these diagnoses, the relevant hospital records will be reviewed for data collection following the women's hospital discharge, death or transfer to another healthcare facility. Data unavailable on the chart but of interest to the study will be obtained from the attending medical team. For each case included, data will be collected on the demographic and obstetric characteristics of the patient, the primary determinant of maternal near-miss (the first complication to occur in the chain of events leading to severe maternal morbidity), the duration of hospitalization (prior to delivery, following delivery and total time), the occurrence of indicators of maternal near-miss at any time during hospitalization, indicators of perinatal outcome and conditions of the woman at discharge from hospital.

These data will be collected on a previously coded form developed specifically for this purpose. A central database will be constructed and the data will be included by the local investigators themselves using electronic forms. The manually completed forms will be filed and made available at technical visits for the purpose of quality control.

For the electronic inclusion of data, each center will have its own restricted area on the study website where password-protected access will be granted only to cases included at that center. An overview of all the cases included in the network will be provided in the form of monthly graphs and tables containing the number of cases included by each center. In addition, the reported diagnoses will be provided by the coordinating center on the main page of the website.

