### Clinical Criteria

Acute cyanosis

Breathing rate > 40 or < 6

Oliguria unresponsive to fluids or diuretics

Loss of consciousness for ≥ 12 hours

Unconscious, no pulse/heartbeat

Jaundice concomitantly with preeclampsia

Gasping

Shock

Coagulation disorders

Cerebrovascular accident

Total paralysis

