### Management Criteria

Use of continuous vasoactive drug

Dialysis for treatment of acute kidney failure

Puerperal hysterectomy due to infection or hemorrhage

Cardiopulmonary resuscitation (CPR)

Transfusion ≥ 5 units of red blood cell concentrate

Intubation and ventilation for a period ≥ 60 minutes, unrelated to anesthesia*

Modified from [5]

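### The organ-dysfunction versus death analysis counts signs that can be part of dying, leaves the outcome of women transferred out unknown, and attaches a confidence interval to a test

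*Protocol article*

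**What the plan says.** One specific objective is "To evaluate the association between the indicators of organ dysfunction used to define maternal near-miss and the risk of maternal death". The Data analysis section gives the method: "The association between organ dysfunction and maternal death will be estimated using odds ratios, likelihood ratio test and their respective 95% confidence intervals".

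The exposure window is set under Data Collection and Procedures, Cross-sectional component, where the items to be abstracted include "the occurrence of indicators of maternal near-miss at any time during hospitalization". Appendix 1 lists the criteria. Its clinical list contains "Unconscious, no pulse/heartbeat" and gasping, and its management list contains cardiopulmonary resuscitation (CPR).

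Under Main outcomes, maternal death is "Death of a woman during pregnancy or within a 42-day period following the end of pregnancy", and a near-miss case must survive. For the cross-sectional component, "the relevant hospital records will be reviewed for data collection following the women's hospital discharge, death or transfer to another healthcare facility". The study population in Methods/Design includes "those who died or were transferred to another healthcare service because of their bad health condition".

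**The concern.** An association between an indicator and death is informative only if the indicator is something other than the death itself. Absent heartbeat is present at every death, gasping may immediately precede one, and CPR is often the response to one. With a window open to the end of the stay and no stated rule separating terminal from earlier dysfunction, these three items can mark the outcome rather than relate to it.

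The outcome has its own problem. It is defined over 42 days, but the data described for each woman stop when she leaves the unit. The women most likely to leave with their fate undecided are those transferred because they were very ill.

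The sentence on method also asks for a confidence interval on a test.

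At stake is the evaluation of the WHO criteria, which Methods/Design gives as a reason for monitoring about 75,000 deliveries to find around 100 deaths and 600 near-miss cases.

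**Working it through.** **The plan's own figures.** Expected count = deliveries × rate.
- Near-miss: 75,000 × 8/1,000 = 600, as stated.
- Deaths: 75,000 × 140/100,000 = 105, against around 100 stated. This is consistent with a rounded figure.

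No effect size or power is given for the odds-ratio analysis.

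**Notation.** OR = (a × d)/(b × c), where a and c are deaths with and without the indicator, and b and d are survivors with and without it. Confidence intervals are Woolf intervals, with 0.5 added to each cell if one is zero. From the document: 100 deaths and 600 near-miss survivors. Everything else below is an assumption, because the documents give no figure.

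**1. Terminal signs, any criterion.** Assume 5,000 survivors without a near-miss criterion (d) and b = 600.

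| Share of deaths counted as exposed | OR | 95% CI |
|---|---|---|
| 80% | 80 × 5,000/(600 × 20) = 33.3 | 20.3 to 54.8 |
| 90% | 90 × 5,000/(600 × 10) = 75.0 | 38.8 to 144.9 |
| 100% | undefined (c = 0); 1,674 with 0.5 added | 104 to 26,981 |

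With d between 1,000 and 10,000, the 80% row runs from 6.7 to 66.7, and the 100% row (0.5 added) from 335 to 3,347. A sign that is part of dying adds exposure only among women who die, so it can only move the estimate down this table. How far depends on how many deaths had no earlier criterion, which is not given.

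**2. Terminal signs, one indicator.** Take CPR and assume 30 of the 600 near-miss survivors positive, so b = 30 and d = 570 + 5,000 = 5,570.
- 10% of deaths recorded positive: 10 × 5,570/(30 × 90) = 20.6
- 30%: 30 × 5,570/(30 × 70) = 79.6
- 90%: 90 × 5,570/(30 × 10) = 1,671

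With 1,000 instead of 5,000 non-near-miss survivors, these become 5.8, 22.4 and 471.

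**3. Deaths after observation ends.** Start from the table with OR 33.3 (80, 600, 20, 5,000). Suppose 10 of the 100 deaths occur after discharge or transfer and are counted as survivals.

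| Share of the 10 with organ dysfunction | Observed OR |
|---|---|
| 20% | 78 × 5,008/(602 × 12) = 54.1 |
| 50% | 75 × 5,005/(605 × 15) = 41.4 |
| 80% | 72 × 5,002/(608 × 18) = 32.9 |
| 100% | 70 × 5,000/(610 × 20) = 28.7 |

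The direction depends on whether the missed deaths carried the indicator more or less often than the observed ones. With 20 missed, all exposed, OR = 60 × 5,000/(620 × 20) = 24.2.

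The other data streams described do not close this gap. Monthly deaths are centre totals. The longitudinal component follows only an invited sample from the second half of the study. Under Ethical aspects, chart data are taken without identifying the woman.

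**4. The statistic.** A likelihood ratio test returns a statistic and a P value. Inverting it gives an interval for the odds ratio, not for the test. Positive and negative likelihood ratios do have confidence intervals and may have been meant, but the text does not say so. This changes no estimate.

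**The case against.** The strongest reply is that the objective is association, not prediction. The any-time window is how a near-miss is classified, and cardiac arrest and CPR belong to the criteria set under evaluation. A narrower window would test a different exposure. Only three of about 25 criteria are affected, and indicator-level estimates would show which. All this is fair, and it is why the three should stay in the analysis but be shown apart. It does not remove the overlap between exposure and outcome in the any-criterion estimate.

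A second reply is that the handling of transfers, and a timing rule, may sit in an analysis plan or in the manual of operation, neither of which is shown. That is possible. But the any-time recording, the close of records at discharge or transfer and the 42-day definition are all stated in the article, and they do not fit together as written.

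Third, the likelihood ratio wording may be a slip in a condensed text. It probably is, and it is easily corrected.

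A reader might infer more than the documents support:
- That all the odds ratios will be inflated. Only the terminal-sign problem has a fixed direction. The outcome problem can go either way, and the wording error biases nothing.
- That transferred women are to be coded as survivors. No passage says so. Their place in the analysis is simply not stated.
- That every death is sure to be charted as meeting the absent-heartbeat criterion. Whether pronouncement of death is recorded that way is not stated.

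**Conclusion.** The point holds in limited form. For absent pulse or heartbeat, gasping and CPR, and for meeting any criterion, terminal recording pushes the odds ratio upward. The size cannot be computed, because the documents do not give the number of non-near-miss survivors or the share of deaths whose only criterion was terminal. The range from 33 to undefined rests on 5,000 such survivors and on 80% to 100% of deaths being exposed.

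For outcome ascertainment, the 42-day definition and the end of individual observation do not match, and women transferred in bad condition have no stated route to a known outcome. The bias has no fixed sign: 29 to 54 around 33, if 10 of 100 deaths are missed and 20% to 100% of those had organ dysfunction. The number of transfers and late deaths is not given.

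The confidence-interval wording is an error of reporting only. None of this invalidates the estimates for the remaining indicators as in-hospital associations.

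**What to change.** 1. Report absent pulse or heartbeat, gasping and CPR separately, and add an any-criterion odds ratio that excludes them beside the one that includes them. Survivors who qualified only on one of the three also lose their exposure in this estimate, so read it as a companion to the full one, not as a bias-corrected value.
2. In the main analysis, do not count women transferred out with unknown outcome as survivors. Add two sensitivity analyses, all alive and all dead. State that outcomes are in-hospital wherever 42-day status is not known.
3. Reword the sentence in Data analysis to odds ratios with 95% confidence intervals and a likelihood ratio test P value. If diagnostic likelihood ratios are meant, specify positive and negative likelihood ratios with 95% confidence intervals.

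Two other remedies may come to mind but are not advised. An exposure window counted back from death defines exposure by the outcome and gives deaths and survivors unequal windows. Linking records between units conflicts with abstraction that does not identify the woman.

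The cost is a little more analysis, probably smaller or less favourable any-criterion odds ratios, and a few women left out of the main analysis. No new data item is required.

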### Results obtained from the preliminary project

Initially, a meeting was held during the Brazilian national congress of Gynecology and Obstetrics in November, 2007, and attended by representatives of 35 healthcare facilities in Brazil. At this meeting, the main points featured in the initial concept of the project were presented and an invitation was made to institutions interested in participating in a Brazilian network on the topic. Those who were interested in participating filled out a registration form with the addresses and characteristics of their respective healthcare institutions. In December 2007, an electronic form was sent to them to be completed with specific information. In accordance with the data received, 27 of these candidate healthcare institutions were selected to participate in the network, taking regional characteristics, geographic distribution, level of complexity and the number of deliveries performed into consideration.

In August 2008, a meeting with representatives from all the centers was held at the coordinating center in Campinas. At this meeting, the proposal was presented and discussed in detail, and suggestions were incorporated into the final version of the protocol. Participating center representatives were identified, the operational issues involved in implementing the study and the theoretical concepts were discussed, and the final version of the research project was defined. Concurrently, a signed commitment was undertaken by each representative to participate in the Brazilian Network for the Surveillance of Severe Maternal Morbidity: the Brazilian Network of Studies in Reproductive and Perinatal Health was created. A Steering Committee was also designated for the study.

### Ethical aspects

The coordinating center has already obtained the approval of the local Institutional Review Board and of the National Council for Ethics in Research (CONEP) of the Brazilian Ministry of Health for both components of the project. The participation of the collaborating centers in this study will only be confirmed after the project has been approved by their respective Institutional Review Boards. Individual signed informed consent will not be requested from the women involved in the cross-sectional analysis, since this study does not involve any type of intervention that could adversely affect their treatment; the data of interest will be obtained retrospectively from the patient's charts and without identifying the woman. Therefore, a waiver of the requirement for signed informed consent was obtained. It is understood that there is no other way of obtaining concrete, reliable information on cases of severe maternal morbidity or death, since these patients are unable to give their consent. However, informed consent will be obtained from the women involved in the longitudinal component of the study. All the principles regulating research in human beings will be respected.

Based on the questionnaires applied, women diagnosed with some type of pathological condition, who are not receiving medical care, will be referred to healthcare facilities equipped to provide them with follow-up care. Women who have already received a diagnosis of a pathological condition but are not being followed up by a physician will also be referred to an appropriate healthcare service.

### Technical and scientific contributions expected from the project

Brazil is a country with very high proportion of births taking place in health facilities (around 97%). The results of the present study will permit a prospective evaluation of severe maternal morbidity and deaths nationwide through the participation of healthcare facilities with different regional characteristics. No multicenter collaborative studies of this dimension are currently being carried out in healthcare institutions in Brazil in the field of Reproductive Health, and no data thus obtained are currently available. In addition to the specific study of maternal health hazards, the organizational structure required by this project will guarantee continuity of the investigation into various conditions of interest to public health beyond the period in which this study will be conducted. The implementation of a collaborative network is essential for expanding the production of substantive research in the field of maternal and perinatal health in Brazil.

Certainly, the availability of resources for the implementation and development of the Brazilian Network for the Surveillance of Severe Maternal Morbidity will lead to new scientific findings relevant to Brazil and other countries. Concomitantly, this will permit the construction of an innovative technological base from which health data may be obtained on a continuous basis, providing the evidence required to institute a real and effective improvement in the quality of life and health of the population. This network is committed to participating in future collaborative studies in the areas of perinatal and women's healthcare. The implementation of a series of multicenter studies is anticipated in this area in a way never before achieved in this country. This fact gives greater power to the results, which will therefore be more representative of the country, a particularly interesting achievement bearing in mind the wide ethnic, cultural and social diversity of the Brazilian population.

We hope that this initiative contributes to the improvement of health care and for the reduction of maternal and perinatal morbidity and mortality.

